## 6.3 Study procedures

The procedures are schematically presented in figure 1. For four times, all participants complete the two taste tests and the MTPRT and fill out the AHSP questionnaire, health related quality of life questionnaire and the supplementary questionnaire. Preoperative the tests and the fulfilment of the questionnaires take place once**.** After the middle ear surgery, the test session will repeat three times; after 1 week, 6 weeks and 6 months. During the preoperative and 1 week postoperative test session also the sniffin’ stick test will take place. Three months after surgery the taste sensation is evaluated at home using the three questionnaires. The other four test sessions will take place during the regular visits of the patient to the hospital. The surgeon will fill out an eCRF about the surgery. The eCRF will be sent by Castor.

*Explanation of the different questionnaires*

- eCRF: 5 multiple choice questions about the middle ear surgery.
- AHSP questionnaire: 33 questions answered on a 5 point Likert scale to assess self-judgement of taste and smell perception. Translated to Dutch and validated in 2001 (36).
- Health related quality of life questionnaire: 24 statements or questions about quality of life ranked by one of the following 6 options: agree, agree partly, disagree partly, disagree, I think this question has no value, I don’t understand the question. 7 questions about depression and anxiety require a yes or no answer. 4 questions answered on a 10 point Likert scale to assess impact of loss of taste function on daily life. This questionnaire is based on the questionnaire of olfactory disorder (37–39).
- Supplementary questionnaire: 5 questions to assess taste perception on a 10 point Likert scale and 10 questions about possible factors that may influence taste sensation.

## 6.4 Withdrawal of individual subjects

Subjects can leave the study at any time for any reason if they wish to do so without any consequences. The investigator can decide to withdraw a subject from the study for urgent medical reasons.

### 6.4.1 Specific criteria for withdrawal

Not applicable.

## 6.5 Replacement of individual subjects after withdrawal

Subjects who withdraw from the study or who terminate the recording session prematurely will be considered as lost to follow-up. To anticipate a withdrawal of 10% of patients, fourteen more patients than needed will be recruited. Therefore, there will be no reason to replace individual subjects after withdrawal, unless more than 10% of participants will withdraw.

## 6.6 Follow-up of subjects withdrawn from treatment

In case of withdrawal, the subject will remain in care of their own otorhinolaryngologist and continue with standard medical treatment.

## 6.7 Premature termination of the study

Serious adverse events (SAE) are not expected, but in case any SAE do occur, each member of the research group has the right to terminate the study prematurely. See also paragraph 8.2.2 Serious adverse events (SAE’s).

# 7. SAFETY REPORTING

## 7.1 Temporary halt for reasons of subject safety

In accordance to section 10, subsection 4, of the WMO, the sponsor will suspend the study if there is sufficient ground that continuation of the study will jeopardise subject health or safety. The sponsor will notify the accredited METC without undue delay of a temporary halt including the reason for such an action. The study will be suspended pending a further positive decision by the accredited METC. The investigator will take care that all subjects are kept informed.

## 7.2 AEs, SAEs and SUSARs

### 7.2.1 Adverse events (AEs)

Adverse events are defined as any undesirable experience occurring to a subject during the study, whether or not considered related to the use of the EGM or TST. All adverse events reported spontaneously by the subject or observed by the investigator or his staff will be recorded in Castor.

### 7.2.2 Serious adverse events (SAEs)

A serious adverse event is any untoward medical occurrence or effect that

- results in death’
- is life threatening (at the time of the event);
- requires hospitalisation or prolongation of existing inpatients’ hospitalisation;
- results in persistent or significant disability or incapacity
- is a congenital anomaly or birth defect; or
- any other important medical event that did not result in any of the outcomes listed above due to medical or surgical intervention but could have been based upon appropriate judgement by the investigator.

An elective hospital admission will not be considered as a serious adverse event.

None of the SAEs are expected as a result of our study. In case, for any unforeseen reason, if the SAE could be due to our study protocol, the study would be paused. An independent team of investigators will be asked to investigate the SAE. In case the independent team of investigators would conclude the SAE would be due to our study protocol, the study will be terminated immediately.

The investigator will report all SAEs to the sponsor without undue delay after obtaining knowledge of the events. The sponsor will report the SAEs through the web portal ToetsingOnline to the accredited METC that approved the protocol, within 7 days of first knowledge for SAEs that result in death or are life threatening followed by a period of maximum of 8 days to complete the initial preliminary report. All other SAEs will be reported within a period of maximum 15 days after the sponsor has first knowledge of the serious adverse events.

7.2.3 Suspected unexpected serious adverse reactions (SUSARs)
Not applicable.

## 7.3 Annual safety report

Not applicable.

## 7.4 Follow-up of adverse events

All AEs will be followed until they have abated, or until a stable situation has been reached. Depending on the event, follow up may require additional tests or medical procedures as indicated, and/or referral to the general physician or a medical specialist. SAEs need to be reported till end of study within the Netherlands, as defined in the protocol.

7.5 [Data Safety Monitoring Board (DSMB) / Safety Committee]
Based on the document Data and Safety Monitoring Board (Groenestyn M.A.C. et. Al, UMCU 7-38) a DSMB is not indicated.

# 8. STATISTICAL ANALYSIS

## All statistical analyses will be performed using the IBM SPSS Statistics version 21.0 software package (Chicago, Illinois, USA). A test for normality and histograms will be used to assess whether variables are normally distributed. We expect limited missing data. Potentially missing variables will be handled with multiple imputation.

## 8.1 Primary study parameter

The primary study parameter is the change in the amount of identified taste strips by patient, preoperatively and 6-8 weeks postoperatively. This outcome will be presented continuous with a range from 1 to 20 identified taste strips. Mean (or the median) and standard deviation (or the range) will be reported. The effect of CTN injury on the amount of identified taste strips will be evaluated using linear regression analysis. The following confounding variables will be included in the analysis: age, gender, smoking, weight, gastroesophageal reflux, olfactory dysfunction, salivary hypofunction, medication, rhinosinusitis/allergic rhinitis, previous COVID-19 and diabetes mellitus (12–22).

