**SUMMARY**

**Rationale:** The chorda tympani nerve (CTN) is a mixed nerve, which carries sensory and parasympathetic fibers. The sensory component supplies the taste sensation of the anterior two-thirds of the ipsilateral side of the tongue. During middle ear surgery the CTN is exposed and frequently stretched or sacrificed, because it lacks a bony covering as it passes the middle ear. The injury may cause hypogeusia, ageusia or altered taste sensation of the ipsilateral side of the tongue. Patients may also suffer from a dry mouth. To date, there is no consensus regarding which type of CTN injury, obtained during primary stapes surgery and primary cochlear implantation, gives the least burden.

**Objective:** To determine whether damaging the CTN during primary stapes surgery and primary cochlear implantation influences postoperative taste function and to determine which type of injury is associated with worse postoperative taste function. Taste function will be measured using taste strips.

**Study design:** A prospective study.

**Study population:** Adult patients, 18 years and older, who are eligible for primary stapes surgery or primary cochlear implantation

**Main study parameter:** Amount of identified taste strips of the ipsilateral tongue to the operated ear (range 0 – 20).

**Nature and extent of the burden and risks associated with participation, benefit and group relatedness:** Patients will not experience any risks during participation in the study. There will be four test sessions. Each time, all participants complete two taste tests and a macronutrient an taste preference ranking task and fill out several sets of questionnaires. The test sessions will take place in the University Medical Center Utrecht during the regular visits of the patient to the hospital. Three months after surgery the taste sensation is evaluated at home using questionnaires. The study burn is moderate. We believe that the burden is in proportion to the potential value of the research.

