# 6. METHODS

## 6.1 Study parameters/endpoints

### 6.1.1 Main study parameter

The main study parameter will be the 6 weeks postoperative amount of identified taste strips of the ipsilateral tongue of the operated ear. The range for possible scores is 0 to 20

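### The protocol defines the primary endpoint in two incompatible ways: a 6-week ipsilateral score in 6.1.1, a change from before surgery in 8.1

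*Protocol*

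**What the plan says.** Section 6.1.1 reads: "The main study parameter will be the 6 weeks postoperative amount of identified taste strips of the ipsilateral tongue of the operated ear". It adds: "The range for possible scores is 0 to 20". The Summary names the same quantity, "Amount of identified taste strips of the ipsilateral tongue to the operated ear", also with a range of 0 to 20, but gives no time point and mentions no change.

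Section 8.1 opens differently: "The primary study parameter is the change in the amount of identified taste strips by patient, preoperatively and 6-8 weeks postoperatively". It says the outcome will be "presented continuous with a range from 1 to 20 identified taste strips". Its model sentence then goes back to the amount: "The effect of CTN injury on the amount of identified taste strips will be evaluated using linear regression analysis". The confounders listed there are "age, gender, smoking, weight, gastroesophageal reflux, olfactory dysfunction, salivary hypofunction, medication, rhinosinusitis/allergic rhinitis, previous COVID-19 and diabetes mellitus". The preoperative taste-strip score is not among them, nor is it among the 12 variables in section 4.4.

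Three other places matter. Section 6.2 states that there is no randomisation. Sections 3 and 5.1 schedule the strip test before surgery and at 1 week, 6 weeks and 6 months, on both sides of the tongue. Section 6.1.2 words the single-taste secondary endpoints explicitly as differences between the preoperative and postoperative ipsilateral scores.

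**The concern.** A postoperative score and a change from baseline are different outcome variables. In a randomised trial both would estimate the same group effect, because the groups have the same expected baseline. Here the injury groups arise during surgery, stapes and cochlear implant patients are pooled, and the model does not hold preoperative taste constant. The two analyses then estimate different quantities, and each can be defended from the protocol as written.

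Two things are at stake. The main result depends on which section the analyst follows. If that choice were open when the data are known, the nominal 5% error rate would no longer apply. A separate analysis plan cannot settle the matter quietly: by following one section it would contradict the other.

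**Working it through.** **1. The two definitions side by side**

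| Element | 6.1.1 (and Summary) | 8.1 |
|---|---|---|
| Quantity | postoperative score | change from preoperative; the model sentence says amount |
| Range | 0 to 20 | 1 to 20 |
| Side | ipsilateral | not stated |
| Time | 6 weeks (none in Summary) | 6-8 weeks |

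**2. Possible ranges.** Section 5.1 gives 5 tastes at 4 concentrations, so one side has 5 × 4 = 20 taste strips and a score from 0 to 20. With two blanks, both sides use 2 × 20 + 2 = 42 strips, the number in the protocol. A change on one side runs from 0 - 20 = -20 to 20 - 0 = +20. A range of 1 to 20 leaves out a score of 0. Read as a change, it leaves out no change and every change in one direction.

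**3. Difference between the coefficients.** Let Y0 and Y1 be the preoperative and 6-week ipsilateral scores, and let X hold the injury categories and the 11 confounders. Least squares is linear in the outcome, so in the same patients

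β(Y1 - Y0) = β(Y1) - β(Y0).

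The two injury coefficients differ by β(Y0), the covariate-adjusted group difference in preoperative score. If that difference is one strip, the two estimates differ by one strip. If Y0 is added to X, the injury coefficient is the same for Y1 and for Y1 - Y0. Only the coefficient of Y0 shifts, by 1.

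**4. Precision.** The protocol gives neither SDs nor the pre-post correlation ρ. Assuming equal SDs before and after surgery, Var(Y1 - Y0)/Var(Y1) = 2(1 - ρ). Adjustment for Y0 leaves a fraction 1 - ρ² of Var(Y1).

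| Assumed ρ | Change / score variance | Standard error ratio | Baseline-adjusted / score variance |
|---|---|---|---|
| 0.3 | 1.4 | 1.18 | 0.91 |
| 0.5 | 1.0 | 1.00 | 0.75 |
| 0.7 | 0.6 | 0.77 | 0.51 |

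**5. Error rate if either version could be reported.** Under the same assumptions the two test statistics correlate at √((1 - ρ)/2) = 0.59, 0.50 and 0.39. For a single contrast, the bivariate normal probability that at least one exceeds 1.96 in absolute value is 0.088, 0.091 and 0.094. This requires both null hypotheses to hold, and hence no adjusted baseline difference.

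**6. Sample size.** Section 4.4 reproduces: 14 degrees of freedom × 10 = 140, plus 14 = 154. The rule uses no effect size, SD or power, so the number is the same under either endpoint. With the preoperative score added, the model has 15 degrees of freedom, and 140/15 = 9.3 patients for each.

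**The case against.** The best defence is that the text leans towards the score. The Summary, 6.1.1 and the model sentence in 8.1 all speak of an amount. Section 6.1.2 shows that the authors write out a difference when they mean one. The range of 1 to 20 looks like a mistyped score range. On this view 8.1 has one discordant sentence and a slip, not a worked-out rival analysis. That is fair as to likely intent. It does not remove the conflict: the discordant sentence is the one that defines the endpoint in the statistical section, and nothing elsewhere overrides it.

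Four stronger readings are tempting, and the document does not support them:

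- **A conflict over the side of the tongue.** A reader might infer that 8.1 means both sides. It omits the side, but its maximum of 20 fits one side only, since two sides would give 40.
- **Two competing time points.** The schedule has a single session at 6 weeks and none at 8. The 6-8 weeks may simply be the window for that visit. Nothing shows that timing differs between the two surgical populations.
- **An actual error rate of 9%.** The figure rests on assumed correlations, on a choice made after seeing the data, and on no baseline difference. That last condition is the opposite of the one that makes the coefficients diverge. Nothing suggests that such a choice is planned.
- **An invalid sample size.** The calculation does not depend on which endpoint is used.

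**Conclusion.** The contradiction between score and change is real, lies in the current protocol text, and must be resolved before analysis. That the coefficients differ by the adjusted preoperative difference is algebra and needs no assumption about the data. How large that difference will be cannot be known from the protocol. The variance ratio of about 1.4 to 0.6 assumes equal SDs and a correlation of 0.3 to 0.7, and the error rate of about 9% is illustrative. The impossible range supports the finding that 8.1 is wrong as written. The unstated side and the 6 versus 6-8 week wording are minor points to align, not separate conflicts.

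**What to change.** Before analysis, state the same quantity, side (ipsilateral), visit with its window, and range in the Summary, 6.1.1 and 8.1. The simplest form is the number of correctly identified strips on the ipsilateral side at the 6-week visit, range 0 to 20, with the preoperative ipsilateral score added to the covariates in 4.4 and 8.1. The choice between score and change then no longer affects the injury coefficient. If the sponsor prefers the change, 8.1 should give its range as -20 to +20, the Summary and 6.1.1 should match, and the role of the preoperative score should be stated.

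The cost is wording and one extra model degree of freedom. Both measurements are already scheduled. Section 4.4 should then report 15 degrees of freedom and about 9.3 evaluable patients for each. Applying the rule of 10 strictly would give 150 + 15 = 165 patients, but restating the figure is enough: the rule is a rough guide, and under the assumptions above the adjustment does not increase the residual variance.

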# 3. STUDY DESIGN

This study concerns a prospective study including patients who will undergo primary stapes surgery or primary cochlear implantation. The study will be performed at the department of Otorhinolaryngology in the UMCU.

The objective of this study is to evaluate the effect of CTN injury on postoperative taste function. CTN injury is a categorical variable with three categories: no touch, mobilisation and completely sectioned.

The study design is illustrated in Figure 1. Patients participate after Informed Consent (IC) is obtained. It will run for approximately two years in the UMCU. Evaluation will take place preoperatively and at 1 week, 6 weeks and 6 months postoperatively by means of taste strip test (TST), electrogustometer (EGM), Macronutrient and Taste Preference Ranking Task (MTPRT) and questionnaires (AHSP questionnaire, Health related quality of life questionnaire and a supplementary questionnaire on taste perception). Preoperatively and 1 week postoperatively the patient’s olfactory function will be evaluated using the Sniffin’ Sticks test. Three months after surgery the taste sensation is evaluated at home using questionnaires. The questionnaires will be sent by Castor or on paper. The contents of these evaluations will be explained in detail in the ‘Investigational products’ and ‘Methods’ section of this protocol.

[figure not shown]

**Figure 1.** Flowchart study procedures. TST: taste strip test, EGM: electrogustometer, AHSP: appetite, hunger and sensory perception, MTPRT: macronutrient and taste preference ranking task The symbol
[figure not shown]
 means that three months after surgery the taste sensation will be evaluated at home using three questionnaires.

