## 4.4 Sample size calculation

We will perform linear regression analysis for our primary outcome measure. Including our potentially confounding covariates, a total of 12 variables will be included in the model. The variables will be injury of the chorda tympani nerve, age, gender, smoking, weight, gastroesophageal reflux, olfactory dysfunction, salivary hypofunction, medication, rhinosinusitis/allergic rhinitis, previous COVID-19 and diabetes mellitus (12–22). We have calculated that these variables are 14 degrees of freedom in total. We will include 10 patients per degree of freedom in our linear regression model. To anticipate withdrawal of 10% of participants, we will include an extra 14 patients which means we will need a sample size of 154 patients.

At the ENT department at the UMCU, 80 otosclerosis patients undergo primary stapes surgery per year and 100 patients undergo cochlear implantation per year. Assuming a participation rate of 70%, we expect to able to include 154 patients in 15 months’ time.

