## 6.2 Randomisation, blinding and treatment allocation

There will be no randomization. The patient and outcome assessor are blinded to the predictor variables, including the presence or absence of CTN injury. The surgeon will complete an electronic Case Report Form (eCRF) in Castor, including the predictor variable CTNinjury. Both patients and researchers will not be informed about the CTN injury until the patient has finished all evaluations. The eCRF will be locked to read for the researchers and the surgeon will not report the CTN injury in the surgery report. After a patient has completed all evaluations, the investigator will read the eCRF and report the CTN injury in the electronic patient record. We do not expect that there are circumstances that require us to unblind the patient or the outcome assessor during the study.

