## 8.2 Secondary study parameters

EGM thresholds and the MTPRT will be reported preoperatively and 1 week, 6 weeks and 6 months postoperatively. The total score and scores of different categories of the questionnaires will be reported preoperatively and 1 week, 6 weeks, 3 months and 6 months postoperatively. The odour identification score will be reported preoperatively and 1 week postoperatively. Mean (or median) and standard deviation (or the range) will be reported. Differences between the different groups of CTN injury will be analysed using linear regression analysis.

Postoperative symptoms of taste disturbance will be analysed using logistic regression analysis, as these outcomes will be presented dichotomously.

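### Linear regression across three CTN-injury groups has no protection against unequal residual variance, and the only stated distribution check would not reveal it

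*Protocol*

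**What the plan says.** Section 8.1 of the protocol fixes the primary method: "The effect of CTN injury on the amount of identified taste strips will be evaluated using linear regression analysis", adjusted for eleven listed covariates. Section 8.2 does the same for EGM thresholds, the food-preference task, the questionnaires and odour identification: "Differences between the different groups of CTN injury will be analysed using linear regression analysis".

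The exposure is defined in section 3: "CTN injury is a categorical variable with three categories: no touch, mobilisation and completely sectioned". Section 6.2 adds: "There will be no randomization". Group sizes therefore depend on what happens in surgery, and the protocol gives no expected split. For the taste-strip score, section 6.1.1 says: "The range for possible scores is 0 to 20".

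The only distribution check is in the opening paragraph of section 8: "A test for normality and histograms will be used to assess whether variables are normally distributed". Its one visible consequence is the choice of summary in section 8.1: "Mean (or the median) and standard deviation (or the range) will be reported". The same paragraph of section 8 names SPSS version 21.0 and multiple imputation.

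The protocol gives no variance estimator for the regression, no group SDs and no residual check. It does not exclude robust standard errors.

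**The concern.** Ordinary least squares estimates one residual variance from all patients and uses it for every contrast between groups. When the true variances differ, that pooled value is too small for some contrasts and too large for others. Unequal group sizes make the error worse.

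Different spreads are plausible here. Mobilisation covers any handling short of section, so outcomes in that group may run from unaffected to badly impaired, while sectioned nerves may give more uniformly low scores.

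The stated check does not address this. The normal-error assumption of linear regression concerns residuals, not raw variables, and a normality test is not a test of equal variance. In a simulation with a correct model (normal errors, common SD 2.5, group means 13/10.2/5, sizes 60/20/60), a Shapiro-Wilk test on the pooled outcome rejected in 80% of runs, only because the group means differ.

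At stake is the accuracy of the intervals and tests for sectioned versus mobilised, and for each versus no touch, which are the contrasts the study exists to estimate.

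**Working it through.** **The plan's own figure.** Section 4.4 says: "We have calculated that these variables are 14 degrees of freedom in total". Ten patients per degree of freedom gives 14 × 10 = 140, and 140 + 14 = 154, as stated. Nothing below changes this. The checks use N = 140 with 2 df for injury and 12 for covariates.

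**Inputs.** From the protocol: three groups, N = 140, 14 df, score range 0 to 20. Assumed, because the protocol gives none: group sizes, group SDs and the 95% level.

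**Formula.** Groups are ordered no touch / mobilised / sectioned. Ignoring covariates:
- pooled variance sp² = Σ(nᵢ − 1)SDᵢ² / (N − 3)
- ratio r = √[ sp²(1/nᵢ + 1/nⱼ) / (SDᵢ²/nᵢ + SDⱼ²/nⱼ) ]
- large-sample coverage of a nominal 95% interval = 2Φ(1.96 r) − 1

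**Equal SDs.** With 3/3/3 at 30/90/20, r = 1 and coverage is 95%. Simulation gives 94.5% to 95.4%. Unequal sizes alone do no harm.

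**Unequal SDs, raw score.** Take SDs 3/4.5/2, so variances 9/20.25/4.

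- Sizes 60/20/60: sp² = (59×9 + 19×20.25 + 59×4)/137 = 8.41.
  - Sectioned vs mobilised: pooled 8.41 × (1/20 + 1/60) = 0.561; true 20.25/20 + 4/60 = 1.079; r = 0.72; coverage 84%.
  - No touch vs mobilised: true 9/60 + 20.25/20 = 1.1625; r = 0.69; coverage 83%.
- Sizes 40/80/20: sp² = (39×9 + 79×20.25 + 19×4)/137 = 14.79.
  - Sectioned vs mobilised: pooled 0.925; true 0.453; r = 1.43; coverage 99.5%.
  - Sectioned vs no touch: pooled 1.110; true 0.425; r = 1.62; coverage 99.8%.

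Simulations of the full 14-df model, with scores rounded and clipped to 0 to 20 and a similar spread for the mobilised group, agree:

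| Sizes | Contrast | OLS coverage |
|---|---|---|
| 60/20/60 | those with mobilised | 83.5% and 85.0% |
| 70/25/45 | those with mobilised | 85.4% and 89.0% |
| 40/80/20 | sectioned vs mobilised | 99.4% |
| 40/80/20 | sectioned vs no touch | 99.8% |

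HC3 covered about 95% to 97%.

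**Change score.** Section 8.1 words the outcome as a change from before surgery, so preoperative variance enters every group and draws the spreads together. As a simple illustration, add an independent preoperative SD of 3 to each group, giving variances 18/29.25/13.

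- Sizes 60/20/60: sp² = 17.41. Sectioned vs mobilised: r = √(1.161/1.679) = 0.83, coverage 90%. No touch vs mobilised: r = √(1.161/1.7625) = 0.81, coverage 89%.
- Sizes 40/80/20: sp² = 23.79. Sectioned vs mobilised: r = √(1.487/1.016) = 1.21, coverage 98.2%. Sectioned vs no touch: r = √(1.785/1.100) = 1.27, coverage 98.7%.

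Simulation of a change score gave about 89% to 98.5%.

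**Other patterns.** In a separate set of nine simulated scenarios (sizes 30/90/20 or 47/47/46, SDs from 1.5 to 5), OLS covered 86.6% to 99.3% and HC3 94.5% to 96.8%. Near-equal sizes (47/47/46) with SDs 2/3/4 still gave 91.5% for mobilised vs sectioned. Mild SD differences gave about 91% to 97.5%. Clipping to 0 to 20 with equal underlying SDs did little: 94.2% to 96.7%.

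**The case against.** The strongest objection is that this rests on silence. The protocol names no variance estimator. Standard errors and residual diagnostics are ordinary content of a statistical analysis plan, which is not shown, and section 10.1 says analysis steps will be documented in an analysis plan. That stands against calling the point an error. What remains is that the method is stated without qualification and the one check stated alongside it cannot show the problem.

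The normality check can also be read as a choice between mean and median, not as a model check. That is the natural reading and there is nothing wrong with that use. It does mean that no stated check looks at the regression.

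Three stronger readings are tempting and unsupported:

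- A reader might infer that the standard errors are wrong. They are wrong only if group variances differ, and the documents give neither SDs nor group sizes.
- A reader might blame the lack of randomisation or the bounded score. Without randomisation, group sizes cannot be fixed in advance, but its main consequence is confounding. The bound alone barely moved coverage. Unequal variance is the driver.
- A reader might infer an inflated false-positive rate. With sizes 50/70/20 and SDs 3/3/4.5, the least-squares test of sectioned vs mobilised rejects about 12% to 13% of the time under no difference. That makes sectioned the most variable group, the reverse of the pattern argued above. With SDs 3/4.5/2 at the same sizes, the rate is 1.0%.

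It is also fair that SDs of 4.5 against 2.0 are a severe contrast (variance ratio 20.25/4 ≈ 5), and that no conclusion has been shown to change. The milder and change-score results are given for that reason. No separate calculation was made for the secondary scores; the point carries over to section 8.2 by the same reasoning.

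**Conclusion.** The point holds conditionally and is a cheap improvement, not the correction of an error. If residual variances differ between injury groups, intervals from unqualified linear regression will be too narrow or too wide depending on which group is small. On assumed values, coverage runs from roughly 84% to 99.8% for a raw score, 89% to 98.5% for a change score and 91% to 97.5% for mild SD differences, against about 95% to 97% with HC3. If the variances are equal, ordinary least squares is fine. All of this rests on assumed SDs and group sizes and on reading linear regression in its usual pooled-variance sense. No figure in the protocol is wrong, and the total of 154 stands.

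**What to change.** In section 8.1, and for the linear models in section 8.2, state that standard errors, confidence intervals and tests for the CTN-injury contrasts will be heteroscedasticity-consistent (for example HC3) and combined across the imputed data sets. In section 8, state that model checks will use residuals, including their spread by injury group, and that the normality check of variables serves only to choose descriptive summaries.

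The cost is two or three sentences and no new data or patients. If the variances are in fact equal, intervals will be about 5% wider than necessary. Availability of the robust option in the named SPSS version, including with multiply imputed data, must be confirmed before the text is fixed.
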